### Participants

*Clusters* Practices in Bavaria will be eligible if they are led by at least one primary care physician and have patients insured by the Allgemeine Ortskrankenkasse Bayern (AOK Bayern), one of the largest health insurance funds in Bavaria with approximately 4.5 millions insured patients. As insured patients are entitled to freely choose their physician and some patients might directly consult medical specialists, neurologists, otorhinolaryngologists and internal medicine specialists will be included in addition to family practitioners.

*Patients* Consenting patients will be eligible for inclusion if they newly consult a participating practice for acute vertigo or dizziness (ICD-10 codes (H81.1–H81.3, H81.8, H81.9, R42 with G63, E53.8, N95.1, G62, I951, H55 or F45.8), are at least 18 years old, and are mentally able to follow instructions. They must also be insured by the AOK Bayern. Patients will be excluded if they are suffering from a mental illness (e.g. dementia), or a terminal disease with a life expectancy of less than 12 months.

### Intervention

The intervention consists of three basic components: a web-based platform (CCDS), a mobile application, and a structured system for continuing medical education, expert support and auditing (see Fig. 1).

**Fig. 1 Fig1:**
[figure not shown]
Summary of the process flow of the intervention. During the study period the German Center for Vertigo and Balance Disorders (DSGZ) will re-assess all patients for the purpose of validating the diagnosis and treatment. Further, the expert network will be established throughout the study period

Patients presenting with acute vertigo at the physician’s office will be eligible for inclusion in the study. After inclusion, the physician (family practitioner, neurologist, otorhinolaryngologist, internal specialist) will use the CCDS. The patient’s answers to a few basic questions (e.g. How long does the vertigo last?), symptoms (e.g. vomiting) and clinical findings (e.g. horizontal nystagmus) will be analysed by an AI-based algorithm. Subsequently suggestions are offered to the physician for a) a categorization of the possible underlying syndrome (e.g. peripheral vs. central vertigo), b) required diagnostic procedures, c) treatment options, and d) referral to physicians with a different medical speciality (e.g. referral from a family practitioner to a neurologist). Additionally, the physician will receive a warning message when symptoms of a severe underlying disease are noted (e.g. skew deviation in cerebral stroke).

Questionnaires and underlying decision algorithms are based on national and international guidelines and the International Classification of Vestibular Disorders (ICVD) of the Bárány Society.

After the diagnostic process has been completed, the patient is given access to a mobile application (app). This application informs the patient about the underlying disease, supports the therapeutic process and monitors the course of the disease. The app is personalized to the patient’s demographic data (age, gender, language, visual impairment) and to the diagnosis. Furthermore, patients will be instructed to fill out a vertigo/dizziness diary on a daily basis. A newly developed, AI-based algorithm then monitors the information gathered from the diary and correlates it with the individual disease. Additionally, an integrated video documentation and analysis system will analyse eye movements and gait abnormalities by the means of pattern recognition (e.g. neuronal networks, deep learning algorithms) [20–22]. It will be used to objectify the diagnosis and classify patient’s self-recorded symptoms.

In case of an unwanted outcome, e.g. signs of a somatization disorder or no visible improvement of symptoms, the app informs the patient and the physician about this development and suggests that the diagnosis and treatment be reconsidered. The physician additionally has access to an expert network for further support.

The expert network will be established throughout the study period. Physicians with special interest in vestibular disorders, taking geographic criteria into consideration, will be selected to participate in interdisciplinary professional training sessions, video-based case review sessions and consultations by phone. The aim is to create a broad network of physicians that are able to correctly diagnose and treat patients with vertigo/dizziness using an interdisciplinary approach. This is especially relevant for rural areas or regions with a sparse medical network. The expert network overall is intended to complement the digital solution.

The anticipated contents of the three main components are summarized in Fig. 2. The intervention will be tested in a 6-month pilot period. Adaptations of the intervention and the contents after this time-period are possible (see below).

**Fig. 2 Fig2:**
[figure not shown]
Contents of the three main components of the intervention: the web-platform with the CCDS, the mobile application, and the educational/support system

### Data collection procedures

Data will be collected at physician (cluster) and patient level. Patient data will be collected at inclusion and after 3 and 6 months. After three months, all patients will be invited to be re-assessed at the German Center for Vertigo and Balance Disorders (DSGZ; see Fig. 1), an outpatient tertiary university unit specialized in the diagnosis and treatment of vertigo and balance disorders. Re-assessments will be blinded to the initial diagnosis and to the study group. Data management will follow the General Data Protection Regulation.

### Measures

The outcomes were chosen to measure the effectiveness, acceptability and efficiency of the intervention at provider (cluster) and patient level.

To measure effectiveness at the provider level, the accuracy of diagnoses made by the primary care physician will be evaluated by re-assessment at the DSGZ. Primary effectiveness outcomes at the patient level will be measured using the Dizziness Handicap Inventory (DHI), a validated instrument for measuring disease-specific quality of life and participation in social life [23]. The DHI scores between 0 and 100, with higher scores indicating a decrease in quality of life. Generic quality of life will be measured using the EuroQol-5D (EQ-5D) [24].

The acceptability and feasibility of the intervention will be assessed using a mixed methods approach. Qualitative data will be ascertained by purposeful sampling through individual and group interviews [25]. Quantitative data will be gathered by questionnaires and standardized documentation of the processes throughout the entire study period (including access data generated from the web-platform and the mobile application).

Efficiency will be assessed in terms of the utilization of health care services and the respective costs. To this end, routine data provided by the health insurer AOK Bayern will be linked to individual patient data from the trial. We will concentrate on outpatient visits, hospitalizations, visits to the emergency room, and imaging, because these seem to be the major cost drivers [26].

### Process evaluation

Process evaluation will be conducted according to the guidelines of the Medical Research Council (MRC) Framework for evaluating complex interventions [27]. During an initial 6-month pilot period, the acceptance and feasibility of the intervention and its components will be evaluated using a mixed-methods approach. In the following main trial (16 months of recruitment of patients) the processes and quality of the implementation will be evaluated. We will evaluate various aspects, including the structure and performance of the included practices, implementation fidelity, satisfaction with the intervention and implementation, assessment of scalability, and documentation and assessment of unexpected effects. Auditing will include quality parameters such as study protocol adherence and number of protocol violations, data quality, and adherence to data protection protocols.

### Harms

The intervention is not expected to lead to any adverse events. Serious unexpected effects believed to be related to the intervention will be collected and recorded according to the GCP from randomization of the first patient through 90 days after the inclusion of the last patient. In this case the intervention will be discontinued, and the patient will be referred to a medical expert.

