## Background

Vertigo and dizziness are amongst the most common key symptoms in medicine. Lifetime prevalence has been shown to lie between 20 and 30% [1, 2]. Claims data from the Bavarian Statutory Health Insurance Physicians’ database showed that over 9% of the adult population received a diagnosis of vertigo annually, most of these in primary care [3]. Disorders of the central or peripheral vestibular system may lead to severe permanent disability or to considerable restrictions of daily life [4]. Although most syndromes—as a rule—can be correctly diagnosed and managed by specialists with interdisciplinary training [5], there is still a large discrepancy between recommended and actual management of patients with vertigo [6, 7]. This might lead not only to overuse of health care resources [4, 8], but also to a prolonged clinical course and to the development of chronic complaints or somatization. Notably, primary care physicians perceive diagnosis and treatment of vertigo as complex and challenging while they feel that they risk missing life-threatening conditions such as stroke or neoplasms [7]. Also, while monitoring symptom evolution under treatment, which is of the utmost relevance for the disease management, it has been noted that the resources of a typical primary care consultation are too limited to closely monitor patients with vertigo. Likewise, the narrow view of single aspects of the underlying disorders reflects the compartmentalization of the clinical specializations (neurology, otorhinolaryngology, internal medicine, etc.) with non-uniform clinical guidelines, and insufficient interdisciplinary cooperation [9].

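### The harm record, limited to serious, unexpected effects believed related to the intervention, has essentially no control-arm comparator and closes about 3 months before the last patients finish follow-up

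*Protocol article*

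**What the plan says.** The Harms section opens with the expectation that "The intervention is not expected to lead to any adverse events". It then sets the capture rule: "Serious unexpected effects believed to be related to the intervention will be collected and recorded". The recording period runs "from randomization of the first patient through 90 days after the inclusion of the last patient". That is a calendar end date common to all patients, not a period counted from each patient's inclusion.

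Other sections bear on this:

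- **Data collection procedures:** "Patient data will be collected at inclusion and after 3 and 6 months". All patients are invited at 3 months to a re-assessment at the specialist centre (DSGZ), blinded to the initial diagnosis and to study group.
- **Measures:** insurer (AOK) data are linked to individual patients. "We will concentrate on outpatient visits, hospitalizations, visits to the emergency room, and imaging". The stated purpose is efficiency, meaning utilisation and cost.
- **Intervention (text after Fig. 1):** the decision system suggests a syndrome category, diagnostic procedures, treatment options and referral, and "the physician will receive a warning message when symptoms of a severe underlying disease are noted".
- **Background:** primary care physicians find vertigo difficult, and "they feel that they risk missing life-threatening conditions such as stroke or neoplasms".
- **Process evaluation:** "In the following main trial (16 months of recruitment of patients"). Unexpected effects are also to be documented and assessed, without further detail.

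**The concern.** A tool that steers work-up and referral in acute vertigo can do harm through omission: a serious cause is missed or found late because the output was reassuring. Such an event may be attributed to the disease and so not counted as related. Because the Background already names it as a known risk, it may also be judged not unexpected. Either judgement keeps it out of the record.

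In the control arm there is no intervention for an event to be related to. A randomised trial would then have a harm record without a comparator, and an empty or short list could not tell whether the programme raised or lowered the rate of missed dangerous diagnoses. This matters here because the Discussion expects savings from fewer diagnostic procedures and consultations.

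The second issue is the end date. Patients who join late are followed for outcomes longer than they are followed for harms.

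**Working it through.** **Inputs.** Harm window: 90 days after the last inclusion (Harms). Follow-up: 6 months (Data collection procedures). Recruitment: 16 months (Process evaluation). Total: 600 patients in 60 clusters, ICC 0.04 (Sample size). Even recruitment is an assumption of this check. A month is taken as 30.4375 days.

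**The plan's own figure.** The Harms section gives no figure beyond the 90 days. The total of 600 reproduces:

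- The t-test with effect size 0.3 needs 175.4, so 176 per arm, or 352.
- Design effect: 1 + (9 − 1) × 0.04 = 1.32.
- 352 × 1.32 = 464.6; 464.6 / 9 = 51.6, rounded up to 52 clusters, or 52 × 9 = 468 patients.
- 52 + 4 + 4 = 60 clusters; 60 × 10 = 600.

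**Capture rule, by arm.**

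| Condition | Intervention arm | Control arm |
|---|---|---|
| Serious | can be met | can be met |
| Unexpected | doubtful for a missed stroke, a named risk | same |
| Believed related to the intervention | can be met, by case judgement | essentially cannot be met |

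All three conditions must hold, so the control count is essentially zero whatever the true event rate.

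**Window.**

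- Follow-up: 6 × 30.4375 = 182.6 days. Recruitment: 16 × 30.4375 = 487 days.
- The last patient is covered for 90 / 182.6 = 49% of follow-up and loses 182.6 − 90 = 92.6 days.
- Everyone included in the last 92.6 days is cut short: 92.6 / 487 = 19.0%; 0.190 × 600 = about 114 patients. In whole months, 3/16 = 18.75%, or about 112.
- Follow-up time lost: (92.6² / 2) / (487 × 182.6) = 4.8%.
- Range if recruitment is uneven: were 10% or 30% of patients included in that last stretch, 60 or 180 would be affected. Their mean loss is about 46.3 / 182.6 = 25% of follow-up, so 2.5% or 7.6% of all follow-up time.

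**What a two-arm comparison could show.** The document gives no rate of missed serious causes. If it were 0.5% to 2% (assumption), 300 patients per arm would yield 300 × 0.005 = 1.5 to 300 × 0.02 = 6 events per arm. Power at 300 per arm to detect 1% versus 2% is about 17%, or 14% with a design effect of 1 + 9 × 0.04 = 1.36. For 2% versus 5% it is 52%, or 40%. Applying the ICC of 0.04 to these events is itself an assumption. Such a comparison is descriptive.

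**The case against.** The strongest reply is that the trial does hold both-arm information on missed serious causes. Diagnostic accuracy, judged by a group-blinded re-assessment to which all patients are invited, is a planned outcome, and a missed serious cause is a diagnostic error. Hospital admissions and emergency visits are linked for individual patients. A reader might infer from the Harms section that missed strokes cannot be compared between arms at all. The documents do not support that, because these sources could be used. What remains is that neither is designated for safety. Re-assessment is by invitation at 3 months, and patients who died or were disabled by a stroke are the least likely to attend.

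Other inferences also go too far:

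- **That an unblinded treating physician judges relatedness.** The Harms section names no assessor.
- **That missing a stroke is physicians' main fear.** The Background reports the fear but does not rank it.
- **That the end date biases the arms against each other.** In a parallel 1:1 design it falls on both arms alike if they recruit at a similar pace. Even the last patient is covered to about the 3-month visit. It is incomplete recording, of modest size.
- **That randomisation of the first patient signals confusion about the unit.** Trial design is clear that practices are randomised, and no analysis hangs on this slip.

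The article also condenses a fuller protocol. Recording is said to follow GCP, and the process evaluation covers unexpected effects without a relatedness condition. Further procedures may exist, but they would not undo the capture rule and end date that the article states outright.

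**Conclusion.** The point holds in this form. Under the stated capture rule the harm record has essentially no control-arm events and therefore no between-arm comparison of serious events. Other both-arm sources could inform one, but the article assigns them to accuracy and cost. This follows from the wording alone and needs no numerical assumption.

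The window falls about 3 months short of the last patients' 6-month visit. That affects about 19% of patients and about 5% of follow-up time, and both figures rest on even recruitment over 16 months. It is the secondary part.

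This should be fixed, but it does not threaten the trial's main result: the DHI outcome, the randomisation and the sample size are untouched. Events will probably be few, so the gain is an interpretable safety table and not a powered test. Without it, a report of no harms would not show safety.

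**What to change.** 1. Record harms for each patient in both arms from that patient's inclusion to the 6-month visit, in place of the common calendar end date.
2. Designate as safety outcomes, regardless of attribution or expectedness: hospital admissions and emergency visits from the AOK linkage; serious causes found at the blinded re-assessment; and, if the extract provides them, deaths and diagnoses of stroke/TIA or another serious cause. Deaths and these diagnoses are not named as planned extracts in the Measures section, so their availability has to be confirmed with the insurer.
3. Report these by arm with cluster-adjusted intervals, as description.
4. Keep the reporting of serious unexpected related effects alongside.
5. As a wording correction only, start the period at inclusion of the first patient instead of that patient's randomisation.

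**Cost.** A few sentences, a table drawn mostly from data already planned, and a query about the extract. The downsides are claims lag, few events with wide intervals, and counts that need interpretation: a correct warning may itself raise admissions and emergency visits, so a higher count in the intervention arm is not automatically harm.

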### Sample size

A difference of 6–10 points in the DHI with a standard deviation of 20 points is assumed to be a relevant clinical difference. This corresponds to an effect size of between 0.3 and 0.5 [6]. A two-sided t-test for independent groups with an effect size of 0.3, an alpha of 0.05 and beta of 0.20 (power = 80%) results in a sample size of *n* = 352 individuals. The inclusion of 10 patients per cluster was assumed with a drop-out rate of 10%, which corresponds to the drop-out rate of similar studies [28, 29]. Therefore, the inclusion of nine patients per cluster was assumed. Taking into account a conservative inter-cluster correlation coefficient (ICC) of 0.04 [30], a design effect (DE) of 1.32 was calculated (DE = 1 + (*k* – 1)  × ICC). This results in a sample size of *n* = 468 patients (234 in the intervention program and 234 in the standard care) and thus 52 clusters. At the level of the clusters, a drop-out rate of 2 clusters per study arm can be expected [31]. To further compensate for possible variations in patient recruitment of the clusters, two additional clusters per study arm were considered. Thus, a total of 60 clusters with 600 patients was calculated.

The additional 6-month pilot phase will include 10 clusters with an expected recruitment of 10 patients per cluster (total *n* = 100 patients; 50 for each study arm). The aim of the pilot phase is to gather information to optimize the study processes (recruitment, randomisation, data gathering, etc.) and to adapt/improve the CCDS and mobile application. The measured outcomes of the pilot phase will not be included in the evaluation and statistical analysis of the main study.

## Discussion

We expect that the intervention will improve the quality and effectiveness of the management of patients presenting with acute vertigo or dizziness.

The intervention is expected to optimize the diagnostic decision process, thus, leading to a timely and more effective therapy and a relevant improvement of patient-relevant outcomes. Also, the mobile application will facilitate treatment adherence and symptom management.

Potential limitations that have to be considered include issues of acceptability and usability of the mobile application and interoperability of the web solution. Special needs of persons with disabilities and older persons will have to be considered. This increased diagnostic accuracy and optimized treatment has the potential to improve long term outcomes and reduce health-care costs by reducing the number of diagnostic procedures, the number of consultations, and the treatment costs.
